## Randomisation

Stroke survivors will receive all-usual treatment for stroke. Participants eligible for inclusion will be identified by a trial investigator. The eligible participants will be initially contacted by telephone and they will be visited in person at their home by the investigator to share the details about the study to the participant and the identified caregiver. A participant information sheet outlining the study objectives, risks and benefits along with brief information sheet about stroke will be provided to the participant. Written informed consent for participation in the intervention will be sought from all participants or from the next of kin if the participant is unable to consent.

An entry form will be used to collect baseline information including the contact details of the participant and the identified caregiver. This information will be forwarded to the independent randomisation centre and the participants eligible for inclusion will be randomised to the intervention or control arm in a 1:1 ratio using a secure, central, password-protected, web-based system. The intervention will be started within 24 hours of randomisation.

## Sample size estimation

The two main factors that determine the number of participants needed in this trial are the estimated event rate and the size of the treatment effect. The primary outcome for the ‘Care for Stroke’ trial is dependency in activities of daily living measured at 6 weeks postrecruitment.

Estimated event rate: in a meta-analysis of early supported discharge trial among participants with stroke, 50% of the stroke survivors were either dead or dependent at the end of follow-up and the beneficial effect of the intervention in the treatment group was an odds reduction of 21% of death and dependency.^26^

As a non-inferiority one-sided trial, to evaluate the effectiveness of the smartphone-enabled educational intervention on dependency, there will be a requirement of 266 participants (133 in each group) to detect a 20% difference in dependency among the participants between the treatment groups with 90% power at the 5% level of statistical significance and with 20% loss to follow-up.

A non-inferiority trial could exclude the possibility of a small degree of inferiority of a new intervention relative to an active control given the sample size. The results of the trial provided by the CI will allow concrete evaluation of the precision actually achieved, superseding any power calculation carried out before the starting the trial.

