## Objective

The objective of the randomised controlled trial is to evaluate whether the ‘Care for Stroke’ intervention is effective for the reduction of dependency in activities of daily living among stroke survivors compared with people receiving standard treatment in an India setting. The primary outcome for the study is disability measured by the modified Rankin Scale (MRS).

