## Intervention arm

The stroke survivor and their caregiver will receive 45–60 min of training on accessing and use of the intervention (watching videos) via the smartphone. Participants will then be provided with a smartphone preloaded with the ‘Care for Stroke’ intervention and asked to try it out on their own. Three or more errorless attempts to retrieve any required part of the intervention from the smartphone will be considered successful training. After successful training, participants will be provided with a smartphone loaded with the intervention and will be asked to use this intervention at their discretion at home over a 6-week period.

The identified caregivers of stroke survivors will be asked to support the stroke survivors as and when necessary to access the intervention from the smartphone. The participants will be telephonically supported at least once in a week during the intervention period. The telephonic support is essentially to remind and obtain updates from the participants or identified caregivers on utilisation of the intervention. A summary of this conversation will be documented and the notes will be kept privately in a locked cupboard. The participants in the intervention arm will not be restricted from receiving standard treatment for their stroke.

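### The sample size section states a one-sided non-inferiority hypothesis with no margin, which contradicts an objective of reducing dependency

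*Protocol article*

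**What the plan says.** The Sample size estimation section frames the calculation "As a non-inferiority one-sided trial, to evaluate the effectiveness of the smartphone-enabled educational intervention on dependency". It then defends the choice: such a trial could "exclude the possibility of a small degree of inferiority of a new intervention relative to an active control". No figure is called a margin. The same sentence gives the requirement of 266 (133 per group) as the number needed "to detect a 20% difference in dependency among the participants between the treatment groups". Power is set at 90%, the significance level at 5% and the allowance for loss at 20%. The background rate comes from a meta-analysis of early supported discharge, in which "50% of the stroke survivors were either dead or dependent at the end of follow-up" and the intervention reduced the odds of that outcome by 21%.

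The Objective section asks whether the intervention is "effective for the reduction of dependency in activities of daily living among stroke survivors compared with people receiving standard treatment". The Abstract and the Methods overview put the aim the same way, and the Introduction calls for a sufficiently powered trial to demonstrate effectiveness.

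On the comparison, the Randomisation section gives usual treatment to all, and the Intervention arm section adds: "The participants in the intervention arm will not be restricted from receiving standard treatment for their stroke". The Analysis section plans an intention-to-treat comparison of MRS 0–3 v 4–6 with an effect estimate and 95% CI. It mentions no margin and no non-inferiority criterion.

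**The concern.** The hypothesis type determines both what the sample size means and what counts as success. Here it is stated twice, once as a label and once with a rationale, and both statements disagree with the objective. The sizing sentence also disagrees with itself, because power to detect a difference is superiority language.

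Non-inferiority suits a new treatment that replaces an active one and may be accepted at a small loss. Here the app appears to come on top of care that both arms can receive. Showing that care with the app is not much worse than care without it would not show that dependency falls. With no margin fixed, one could also be chosen or inferred after the results are known, and a trial with more dependent patients in the app arm could be reported as a success.

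**Working it through.** **Inputs.** All come from the Sample size estimation section: 50% dead or dependent, a 20% difference, one-sided 5% (z = 1.645), 90% power (z = 1.2816), 20% loss, 133 per arm. I read the 20% as percentage points; the protocol does not say.

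**Reproducing 133 per arm.** Two routes come close.

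- Non-inferiority, 50% in both arms, 20-point margin: n = (1.645 + 1.2816)² × 2 × 0.25 / 0.20² = 107.05. Allowing for loss, 107.05 / 0.8 = 133.8. Rounding up at each step gives 108, then 135.
- Superiority, 50% v 30%, one-sided 5%: n = [1.645√(2 × 0.4 × 0.6) + 1.2816√(0.25 + 0.21)]² / 0.20² = 100.9. The continuity correction, (n/4)[1 + √(1 + 4/(0.20n))]², gives 110.65. Multiplying by 1.2 gives 132.8, so 133 per arm and 266 in total. Multiplying by 1.2 is a common but incorrect allowance for 20% loss; dividing by 0.8 gives 139.

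The number therefore does not reveal which hypothesis was used. A relative reading of 20% (50% v 40%) does not fit: with loss it needs 529 per arm one-sided or 649 two-sided.

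**If the 20% is the margin.** Evaluable per arm: 133 × 0.8 ≈ 106. SE of the difference near 50%: √(0.5/106) = 0.0687.

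- Cited benefit: odds of 1 × 0.79 give 0.79/1.79 = 44.1%, a fall of 5.9 points. Ratio: 20 / 5.87 ≈ 3.4.
- Largest observed excess of dependency that still passes: 20 − 1.645 × 6.87 = 8.7 points by a one-sided 5% rule, and 20 − 1.96 × 6.87 = 6.5 points by the planned 95% CI.
- Chance of declaring non-inferiority, Φ[(limit − true excess)/SE]:

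| True excess | One-sided 5% | 95% CI |
|---|---|---|
| 5.9 points | 66% | 54% |
| 10 points | 43% | 31% |

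**Level and interval.** A one-sided 5% test corresponds to a 90% CI. The planned 95% CI corresponds to one-sided 2.5%, so the sizing and the analysis use different error rates.

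**266 as a two-sided 5% superiority trial.** Power = Φ{[d − 1.96√(2p̄(1 − p̄)/106)] / √[(p₁(1 − p₁) + p₂(1 − p₂))/106]}.

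- 50% v 30%: (0.200 − 0.1319)/0.0659 = 1.03, power about 85%.
- 50% v 44.1%: (0.0587 − 0.1344)/0.0684 = −1.11, power about 13%.
- For 90% power at 50% v 30%: [1.96 × 0.6928 + 1.2816 × 0.6782]² / 0.04 = 124 per arm; 124/0.8 = 155; 310 in total.

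**The case against.** The strongest reply is that the Analysis section plans no non-inferiority test. It plans an intention-to-treat estimate with a 95% CI, and the sample size section says that the interval will supersede any power calculation. If that interval excludes no difference, it shows reduced dependency whatever the label. This stands. A reader might infer that the trial as planned cannot answer its own question, and the documents do not support that. The inability belongs to a non-inferiority conclusion, not to the data.

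A reader might also take 266 as proof that a non-inferiority test with a 20-point margin was intended. That is not supported either: the protocol never calls 20% a margin, and a superiority route gives 266 exactly. The tolerated excesses and pass rates above are therefore conditional.

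It could be said that non-inferiority has a purpose if families use the app in place of therapy, since the protocol also asks whether it lowers the overall cost of care. The protocol does not make that argument. Equally, it does not use the term add-on; I infer that from usual treatment being open to both arms.

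It is tempting to add that intention-to-treat alone is weak for non-inferiority. I do not press this. It suits superiority, and further analysis sets may be in an analysis plan that is not shown.

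None of this removes the contradiction. The statement about the interval concerns precision and does not say which hypothesis is tested. Nor is this a detail left to the analysis plan, because the protocol states the hypothesis and states it against its own objective.

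**Conclusion.** The point holds as a contradiction that must be fixed. The stated hypothesis (one-sided non-inferiority, no margin) is wrong for the stated objective and for a comparison in which both arms may receive usual care. The one-sided 5% level does not match the planned 95% CI. These conclusions rest on the text alone.

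The size is conditional. If the 20% is an absolute margin and dependency is near 50%, the margin is about 3.4 times the cited 5.9-point benefit, hardly a small degree of inferiority. Success could then be declared with up to 8.7 points (one-sided 5%) or 6.5 points (95% CI) more dependency observed in the app arm. If 266 came instead from a superiority calculation, the label is simply false and must still go.

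**What to change.** Delete the non-inferiority and one-sided wording from the Sample size estimation section, including the paragraph sentence that justifies it. State the primary hypothesis as superiority: a two-sided 5% comparison of the proportion with MRS 4–6 at 6 weeks, by intention to treat, with effectiveness claimed only if the planned 95% CI excludes no difference.

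Keep 266, but restate what it provides at about 106 evaluable per arm: about 85% power for 50% v 30%, and about 13% for the cited 21% odds reduction. Say that the 20% is in percentage points, if that is what was meant.

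The cost is wording; conduct, outcome and the planned estimate are unchanged. The price is candour about power. The stated figure falls from 90% to about 85% for a 20-point difference (restoring 90% would need about 310 in total), and the protocol must acknowledge low power for the effect it cites.

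### The 90% power belongs to an unexplained 20-point difference or margin, not to the 21% odds reduction that is the section's only evidence on effect size

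*Protocol article*

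**What the plan says.** The Sample size estimation section of the protocol article names the event rate and the size of the treatment effect as the two things that fix the number of participants. Its evidence on both comes from one meta-analysis of early supported discharge trials. On effect size it reports that "the beneficial effect of the intervention in the treatment group was an odds reduction of 21% of death and dependency". For the event rate it gives this figure: "50% of the stroke survivors were either dead or dependent at the end of follow-up".

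The next paragraph opens with "As a non-inferiority one-sided trial". It sets the total at 266, or 133 per arm, and describes the target as "to detect a 20% difference in dependency among the participants between the treatment groups with 90% power at the 5% level of statistical significance". Attrition is allowed for at 20%. The paragraph does not say whether the 20% difference is absolute, relative or on the odds scale, or whether it is an effect to be shown or a margin to be excluded. It gives no source for the figure.

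The Objective section asks whether the intervention reduces dependency compared with standard treatment. The Analysis section reports the dichotomised primary outcome as an effect estimate with a 95% CI.

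**The concern.** A reader who sees a 21% odds reduction followed by a 20% difference will take the two as roughly the same effect, and the 90% as the chance of detecting it. They are on different scales. At a 50% control rate, 20 absolute points is about 3.4 times the cited effect (20 / 5.87).

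At stake is how the result will be read. The Objective is a reduction in dependency. If the true benefit is of the cited size, a trial of 266 will usually give an interval that includes zero, and the quoted 90% would lend that result more weight against the intervention than it deserves.

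**Working it through.** **Inputs**, all from Sample size estimation except where noted: control rate 50%; cited odds reduction 21% (OR 0.79); 20% difference; power 90% (z = 1.282); one-sided 5% (z = 1.645); loss 20%; 133 per arm. Evaluable per arm: 133 × 0.8 = 106.4, taken as 106. Two-sided 5% (z = 1.960) is shown as well because the Analysis section reports a 95% CI.

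**1. The cited effect on the risk scale.** Odds at 50% are 1. After a 21% reduction they are 0.79, so the risk is 0.79 / 1.79 = 44.1%. The difference is 5.9 points.

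**2. Reproducing 266.** For a difference between p1 and p2 with mean p̄, n per arm = [zα√(2p̄(1−p̄)) + zβ√(p1(1−p1) + p2(1−p2))]² / (p1−p2)². For a margin m with equal rates p, n per arm = 2p(1−p)(zα + zβ)² / m².

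| Reading of the 20% (one-sided 5%, 90% power) | Evaluable per arm | Total after loss |
|---|---|---|
| 60% v 40% | 105.2 (106 in some routines) | /0.8: 263 to 266 |
| 20-point margin, 50% in both arms | 0.5 × 8.564 / 0.04 = 107.0 | /0.8: 268 |
| 50% v 30%, continuity correction | 110.7 (111) | ×1.2: 266 to 268 |
| 50% v 30%, no correction | 100.9 (101) | /0.8: 252 to 254 |
| 20% relative, 50% v 40% | 422 | /0.8: about 1,055 |
| Cited OR 0.79, 50% v 44.1% | 1,238 | /0.8: about 3,096 |

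The first three rows come close to 266, and all use 20 absolute points. No relative or odds-based reading comes near it. Because three routes fit, the document does not reveal which one was used.

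**3. Power to show a reduction with 106 evaluable per arm.** Power = Φ{[(p1−p2)√n − zα√(2p̄(1−p̄))] / √(p1(1−p1) + p2(1−p2))}.

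| True rates | One-sided 5% | Two-sided 5% |
|---|---|---|
| 50% v 44.1% (cited effect) | 21.5% | 13.4% |
| 50% v 40% (20% relative) | 42.8% | 30.9% |
| 50% v 30% (20 points) | 91.2% | 84.9% |

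**4. Power for non-inferiority, if the 20 points are a margin.** Power = Φ{(m + p1 − p2) / SE − 1.645}.
- At zero true difference, SE = √(0.5/106) = 0.0687, which gives Φ(2.91 − 1.645) = 90%.
- At the cited effect, SE = √[(0.25 + 0.2466)/106] = 0.0684, which gives Φ(0.2587/0.0684 − 1.645) = Φ(2.13), about 98%.

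**5. Precision and minimum detectable difference.** The 95% CI half-width near 50% is 1.96 × 0.0687 = 0.135, so about 13 points. Solving the power formula in step 3 for the difference, two-sided and from 50%, gives about 19 points (18.8) at 80% power and 21.5 points at 90%.

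**The case against.** The strongest reply is that the section calls the trial a one-sided non-inferiority trial. A 20-point margin with equal rates gives about 268, which is as good a match as any. On that reading the 90% is the power to exclude 20-point harm when there is no true difference, and the trial has about 98% power for non-inferiority if the cited effect is real. This stands. A reader might infer that the trial would almost certainly fail if the cited effect were true, but that holds only for showing the reduction named in the Objective. Even so, the 90% is still not the power for the cited effect.

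A second reply is that the 21% appears in the paragraph on the event rate, comes from a different intervention, and that a trial may be powered for a larger effect than an analogue showed. This stands in part. Reliance on the 21% is an inference, though the section names effect size as a driver and offers no other evidence on it. A reader might also infer that the 21% odds reduction was mistakenly carried over as 20 absolute points. The closeness of the two figures suggests it, but nothing in the document says so.

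A reader might further infer that the target was 50% to 30%. The document never states 30%, and the plain calculation for it gives about 252 rather than 266.

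Finally, the section itself says that the CI will supersede any prior power calculation, and nothing says that a null result will be reported as no effect. That reduces the risk of misreading but does not correct the power statement.

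**Conclusion.** The point holds as an unspecified and unsupported 20% whose stated power does not apply to the effect cited beside it. It is not an arithmetic failure, since 266 can be approached, but only with 20 absolute points. Against the 5.9 points that the cited evidence implies, power to show a reduction is about 21% one-sided or 13% two-sided.

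These figures assume a 50% control rate (as cited), the full 20% loss and a simple comparison of two proportions. With no loss (133 per arm) they rise only to about 25% and 16%. The conclusion does not depend on which 20-point reading was used, or on how the 20% was chosen. Whether the trial is meant to show superiority or non-inferiority is left open here; the size of the shortfall applies to superiority only.

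**What to change.** Keep 266 and revise the Sample size estimation section as follows:

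- State that the 20% is 20 absolute percentage points, give the control rate actually used, and say whether it is a superiority effect or a non-inferiority margin, with a justification. The sponsor must supply these; 50% to 30% should not be presumed.
- Stop presenting the 21% odds reduction as the basis for the 20%.
- Report the power to show a reduction at the cited effect (about 21% one-sided, 13% two-sided) and the minimum detectable difference (two-sided from 50%: about 19 points at 80% power, 21.5 at 90%).
- State in the Analysis section that a 95% CI containing both zero and a 6-point benefit will be reported as inconclusive on superiority.

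The cost is wording only, with no extra participants. The downside is that the stated power becomes less favourable.

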**Methods:**

The objective of the study is to evaluate whether the ‘Care for Stroke’ intervention is clinically and cost-effective for the reduction of dependency in activities of daily living among stroke survivors in an Indian setting. This study is designed as a randomised controlled trial comparing people who received the intervention to those receiving standard care. The trial will be pragmatic and outcome assessor-blinded. The primary outcome for the study is dependency in daily living measured by the Modified Rankin Scale (MRS). A total of 266 adult stroke survivors who fulfil the eligibility criteria will be randomised to receive either ‘Care for Stroke’ intervention or standard treatment and will be followed up for 6 weeks. The main analyses will compare participants allocated to the ‘Care for Stroke’ intervention versus those allocated to the standard treatment group on an ‘intention-to-treat’ basis, irrespective of whether the participants received the treatment allocated or not. The dichotomised MRS scores (0–3 and 4–6) in both the groups will be used to calculate the effect estimates with a measure of precision (95% CI) and presented in the results of the trial.

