## Analysis

The main analyses will compare all those allocated to the ‘Care for Stroke’ intervention with those allocated to the standard treatment group on an ‘intention-to-treat’ basis, irrespective of whether the participants received the treatment allocated or not. The imbalance in recruiting equal number of participants if any will be addressed during the analysis phase using appropriate statistical techniques. The dichotomised MRS scores (0–3 and 4–6) in both the groups will be used to calculate the effect estimates with a measure of precision (95% CI) and presented in the results of the trial. Subgroup analysis for the primary outcome will be based on stroke severity, location of the participant (urban/rural), gender and age at stroke. Interaction tests will also be used to test whether the effect of treatment (if any) differs across these subgroups.

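### The 90% power is correct for the declared one-sided 5% test, but the only interval named for the primary outcome is a 95% CI, for which 266 participants with 20% loss give about 81–85%

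*Protocol article*

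**What the plan says.** All the sizing inputs are in the Sample size estimation section of the protocol article:

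- Design and sidedness: "As a non-inferiority one-sided trial, to evaluate the effectiveness of the smartphone-enabled educational intervention on dependency".
- Event rate, taken from a meta-analysis of early supported discharge: "50% of the stroke survivors were either dead or dependent at the end of follow-up".
- Effect: "to detect a 20% difference in dependency among the participants between the treatment groups". The text does not say whether this is absolute or relative, and no non-inferiority margin is named as such.
- Error rates and loss: "with 90% power at the 5% level of statistical significance and with 20% loss to follow-up".
- Result: 266 participants, 133 per arm, allocated 1:1.

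The same section adds that the CI will show the precision achieved and will take precedence over the prior power calculation.

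For the analysis, the Analysis section says that the MRS split at 0–3 v 4–6 will be used to "calculate the effect estimates with a measure of precision (95% CI"). The Methods paragraph of the abstract says the same. Neither place mentions a 90% CI, a one-sided bound or a one-sided test.

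**The concern.** A reader who sees 90% power at the 5% level in one section and a 95% CI in another will take the two to correspond. They do not. A one-sided 5% test matches a one-sided 95% bound, which is a limit of the two-sided 90% CI. A conventional 95% CI is stricter, with 2.5% on each side. If the primary comparison is read from the 95% CI, the chance of missing the planned effect is larger than the 10% that the sizing implies, and an inconclusive interval would carry less evidence against the intervention than a stated 90% suggests.

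**Working it through.** **Inputs.** From Sample size estimation: control proportion 50%, difference 20%, power 90%, 5% one-sided, loss 20%, 133 per arm. Assumption: the difference is 20 percentage points, so superiority is 50% v 30%. On the non-inferiority reading the margin is 20 points with 50% in both arms. Evaluable per arm: 133 × 0.8 = 106.4, taken as 106.

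**1. Reproducing 266.** Superiority, pooled-variance formula:

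n = [z_α √(2·p̄·q̄) + z_β √(p₁q₁ + p₂q₂)]² / d², with √(2 × 0.4 × 0.6) = 0.6928, √(0.25 + 0.21) = 0.6782, d = 0.20, z_β = 1.2816.

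- One-sided 5%: (1.645 × 0.6928 + 1.2816 × 0.6782)² / 0.04 = 100.9 per arm. With continuity correction, (n/4)(1 + √(1 + 4/(nd)))² = 110.7, rounded up to 111.
- Two-sided 5%: (1.960 × 0.6928 + 1.2816 × 0.6782)² / 0.04 = 124.0; with continuity correction 133.8.

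Non-inferiority: n = (1.645 + 1.2816)² × 0.5 / 0.04 = 107.05 per arm.

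Three routes arrive at about 133 per arm:

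| Route | Per arm |
|---|---|
| Non-inferiority, one-sided 5%, divided by 0.8 | 107.05 / 0.8 = 133.8 |
| 50% v 30%, one-sided 5%, continuity-corrected, multiplied by 1.2 | 111 × 1.2 = 133.2 |
| 50% v 30%, two-sided 5%, continuity-corrected, no allowance for loss | 133.8 |

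The document does not say which was used. No two-sided superiority variant that includes 20% loss gives 266; they run from 298 to 336. A relative reading (50% v 40%) needs at least 846 in total before any loss, so it does not reproduce 266.

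**2. Power at 106 per arm, 50% v 30%.** z_β = (0.20 × √106 − z_α × 0.6928) / 0.6782, with 0.20 × √106 = 2.0591.

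- One-sided 5%: (2.0591 − 1.1396) / 0.6782 = 1.356, power 91.2%.
- 95% CI: (2.0591 − 1.3579) / 0.6782 = 1.034, power 84.9%.

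With continuity correction, inverting the correction gives an effective n of (106 − 1/0.20)² / 106 = 96.2. The powers become 88.7% and 81.4%.

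Exact enumeration agrees: a Wald 95% CI excludes zero with probability 85.9%, and the two-sided Fisher test has 81.6% power.

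**3. Power at 106 per arm, non-inferiority.** Standard error = √(0.5/106) = 0.0687, and 0.20 / 0.0687 = 2.912.

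- One-sided 5%: 2.912 − 1.645 = 1.267, power 89.7%.
- 95% CI: 2.912 − 1.960 = 0.952, power 82.9%.

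**4. If 266 was a two-sided size.** With no loss, 133 per arm gives 91.9% two-sided (89.8% corrected). The stated 20% loss is then not covered, and the corrected power after loss is the same 81%.

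**5. For comparison: randomised total for 90% power with the 95% CI and 20% loss.** 124 / 0.8 = 155 per arm, 310 in total; with continuity correction 134 / 0.8 = 167.5, 336 in total; non-inferiority 132 / 0.8 = 165, 330 in total.

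**The case against.** The strongest reply is that nothing has been miscalculated. The section declares a one-sided trial at 5%, and for that test 106 per arm give 89–91% power. This stands: the 90% is not an arithmetic error, and the sidedness of the sizing is already stated. What is missing is agreement between that test and the interval.

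A second reply is that the 95% CI is described as a measure of precision, not as a decision rule. This also stands in part. A reader might infer that success will be judged by whether the 95% CI excludes a value, but no section says so, and a formal rule may sit in an analysis plan that is not shown. The lower power therefore applies if the conclusion is drawn from the 95% CI. Since that is the only inferential output named, and the sizing section tells the reader to rely on the CI over the power calculation, the mismatch still needs resolving in this document.

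Other stronger readings are tempting and are not supported:

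- That 266 can come only from a one-sided calculation. A two-sided continuity-corrected size without loss gives the same number.
- That loss was inflated wrongly, by multiplying by 1.2. That is only one of three routes; another divides by 0.8.
- That 20% certainly means 20 percentage points. The text does not say. If it were relative, 50% v 40%, two-sided power at 106 per arm would be only about 31%.

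**Conclusion.** The point holds as an inconsistency of moderate importance, not as an error in the 90%. The sizing is at one-sided 5%; the named interval corresponds to one-sided 2.5%. At 106 evaluable per arm the power for the 95% CI is about 85% (81% with continuity correction) for 50% v 30%, and about 83% for non-inferiority with a 20-point margin. The risk of missing the planned effect is thus about 15–19% on either hypothesis, against a stated 10%.

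This rests on three assumptions: the 20% is absolute and starts from 50%; the 95% CI is two-sided, as is conventional; and loss is the stated 20%. The shortfall does not hinge on the exact base rate: at 60% v 40% the two-sided power is 83% (80% corrected). Nor does it depend on how 266 was obtained. All these figures are for the planned 20-point difference; whether that difference is realistic is a separate question.

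**What to change.** Keep 266 and make the sizing and the interval agree. The sponsor first confirms which hypothesis is primary, because a restated power must not turn the declared non-inferiority design into two-sided superiority without saying so. Then take one of two courses.

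1. **Keep the 95% CI and restate the power.**
   - *Superiority:* with 266 randomised and 20% loss (106 analysed per arm), power is about 85% (81% with continuity correction) for the two-sided 95% CI to exclude no difference if the true proportions with MRS 4–6 are 50% and 30%.
   - *Non-inferiority:* with the same numbers, power is about 83% for the 95% CI to exclude a 20-point disadvantage if both true proportions are 50%.
2. **Keep 90% and change the interval used for the conclusion.** State in Sample size estimation, in Analysis and in the abstract that the primary conclusion is read from a one-sided 95% bound, that is, a limit of the two-sided 90% CI. A 95% CI may still be shown as description.

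In either case, say that the 20% is an absolute difference and confirm that 266 already includes the 20% loss.

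The cost is a few reworded sentences. The first course carries a less favourable power figure; the second openly accepts a 5% one-sided error rate. Neither adds participants.
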